## Abstract

**Background:**

Significant disparities continue to exist in the HIV care continuum, whereby Hispanic and Black people living with HIV (PLWH) are less likely to achieve viral suppression compared to their White counterparts. Studies have shown that intervention approaches that involve peer navigation may play an important role in supporting patients to stay engaged in HIV care. However, implementation may be challenging in real-world settings where there are limited resources to support peer navigators. Combining a peer navigation approach with scalable mobile health (mHealth) technology may improve impact and implementation outcomes.

**Methods:**

We combined a peer navigation intervention with a mHealth application and are conducting a randomized controlled trial (RCT) to test the efficacy of this integrated “Peers plus mobile App for Treatment in HIV” (PATH) intervention to improve HIV care engagement, and ultimately sustained viral suppression, among Hispanic and Black PLWH. We will enroll up to 375 PLWH into a two-arm prospective RCT, conducting follow-up assessments every 3 months up to 12 months post-baseline. Participants randomized to the control arm will continue to receive usual care Ryan White Program case management services. Individuals randomized to receive the PATH intervention will receive usual care plus access to two main intervention components: (1) a peer navigation program and (2) a mHealth web application. The primary outcome is sustained HIV viral suppression (undetectable viral load observed at 6- and 12-month follow-up). Secondary outcomes are retention in HIV care, gaps in HIV medical visits, and self-reported ART adherence. Recruitment for the RCT began in November 2021 and will continue until June 2024. Follow-up assessments and medical chart abstractions will be conducted to collect measurements of outcome variables.

**Discussion:**

The efficacy trial of PATH will help to fill gaps in our scientific understanding of how a combined peer navigation and mHealth approach may produce effects on HIV care outcomes while addressing potential implementation challenges of peer navigation in Ryan White-funded clinics.

**Trial registration:**

The PATH trial is registered at the United States National Institutes of Health National Library of Medicine (ClinicalTrials.gov) under ID # NCT05427318. Registered on 22 June 2022.

## Introduction

### Background and rationale {6a}

Significant disparities continue to exist in the HIV care continuum, whereby Hispanic and Black women and men living with HIV are less likely to achieve viral suppression compared to White women and men living with HIV [1–7]. In 2016, among people living with HIV (PLWH) aged 13–29, an estimated 42% of Blacks/African Americans and 36% of Hispanics in the US were not virally suppressed [8]. Disparities are exacerbated by co-occurring syndemic conditions, including substance use and mental health conditions [9–11]. As elsewhere, substance use is a robust correlate of HIV infection in San Diego [12, 13], especially near the Mexico border where methamphetamine and opioids are trafficked and readily accessible [14]. Therefore, interventions to promote viral suppression among PLWH must be developed and tested in the most vulnerable, lower-resourced communities, including communities affected by substance use.

Community health workers, and particularly peer navigators (also referred to as peers, “promotoras/es,” or “compañeros/as de apoyo”), have been shown to play meaningful roles in supporting patients living with HIV to stay engaged in care in developing countries [15, 16]. The evidence base is smaller in the US. A 2016 systematic review of interventions involving PLWH serving as peers to improve HIV care continuum outcomes identified nine published studies [17]. Only a minority (44%) were in the US with the rest (56%) in sub-Saharan Africa. While six of the nine used a randomized controlled trial (RCT) design, only one study found a positive effect on viral suppression. Further, only two of the four interventions in the US were tested with a sample who were predominantly racial/ethnic minority, but neither specified addressing barriers to HIV care unique to Hispanic and Black PLWH (i.e., stigma, medical mistrust). The findings from this review suggest that more studies applying a rigorous design are needed to evaluate the impact of peer navigation on HIV care continuum outcomes in the US, particularly to address barriers unique to racial/ethnic minorities living with HIV [18–20].

While peer navigation may promote positive health outcomes among PLWH, implementation and scale-up of this approach may encounter difficulties in real-world clinical and community settings where there are limited resources to support peer navigation programs [21, 22]. In contrast, mobile health (mHealth) is a scalable approach that can be more feasibly implemented since it requires fewer staff resources [23, 24]. To further illustrate, a clinic may require a large team of peer navigators to adequately support an entire caseload of patients with HIV. However, when combined with mHealth, the impact that peer navigators can have on supporting people with HIV may be strengthened. Thus, combining peer navigation and mHealth intervention approaches may be one strategy to simultaneously reduce the need for larger teams of peer navigators, while also strengthening the impact of peer navigation on HIV care continuum outcomes among Hispanic and Black PLWH. mHealth and other technologies offer platforms for intervention delivery through various devices, such as laptops, tablets, smartphones, and channels, such as online, mobile apps, SMS, and social networking platforms, to overcome the limitations and costs of in-person interventions [23, 24]. In a systematic review of mHealth interventions designed for racial/ethnic minority groups, those that focused on HIV were aimed at HIV primary prevention, with only two focused on HIV care self-management, with text message reminders to support antiretroviral therapy (ART) adherence [25]. Also, a review of mHealth interventions to support self-management in HIV found that of the 28 interventions identified, the majority (57%) used text messaging, and only 5 (18%) used mHealth applications (apps) [26]. Of the five mobile app interventions, none appeared to be tailored to address challenges, such as stigma and substance use [26], experienced by Hispanic and Black PLWH. Altogether, the evidence suggests that there is a critical absence of rigorous, randomized controlled trial (RCT) studies in the US to evaluate the efficacy of peer navigation and mHealth intervention approaches to improve viral suppression and retention in HIV care among Hispanic and Black PLWH.

Combining both peer navigation and mHealth technology into a unified, scalable intervention could both strengthen the impact of peer navigation on HIV care outcomes among PLWH and simultaneously reduce the amount of resources needed to support peer navigation in clinical settings, effectively striking the needed balance between clinical effect sizes and implementation costs [27]. In this trial, we propose the Peers plus mobile App for Treatment in HIV (PATH) intervention that may serve as an integrated solution that builds on the strengths of peer navigation to improve HIV care engagement and ART adherence, while also addressing potential implementation challenges of peer navigation.

## Objectives {7}

The primary goal of this RCT is to evaluate the efficacy of the PATH intervention compared to usual care in a community-based HIV care setting on our pre-defined primary and secondary outcomes. Specific aims are threefold: (1) examine efficacy of PATH on primary (viral suppression at 6 and 12 months) and secondary outcomes (retention in HIV care; gaps in HIV medical visits; self-reported ART adherence); (2) examine the theory-informed mediators (e.g., increased self-efficacy to engage in HIV care, and reduced medical mistrust and HIV stigma), through which PATH may have the greatest impact on outcomes among Hispanic and Black PLWH; and (3) among those using substances, explore whether PATH significantly affects substance-related outcomes, including frequency of substance use and engagement in substance use treatment, when compared to usual care (UC). A sub-aim of the trial is to explore subgroup differences in efficacy based on factors such as race/ethnicity and substance use.

## Trial design {8}

We are implementing a two-arm parallel group randomized controlled superiority trial design, whereby enrolled participants complete a baseline assessment, and then are randomized on a 1:1 ratio into one of two arms. In the control arm, participants receive UC Ryan White coordinated case management services (i.e., standard intake and as needed, referrals medical, dental and mental health services, case management, and alcohol/substance use treatment]). In the PATH intervention arm, participants receive UC plus two main intervention components: (1) support from a peer navigation program and (2) access to the PATH mHealth web application. Post-baseline/randomization, participants are asked to complete follow-up assessments at 3, 6, 9, and 12 months.

## Methods: participants, interventions, and outcomes

### Study setting {9}

The RCT is being implemented in a community-based federally qualified health center (FQHC) located in the southern part of San Diego County, CA, along the US-Mexico border. This FQHC offers HIV primary and sub-specialty medical services and coordinated case management services at multiple locations to a majority racial minority population, which will help achieve the study goal of reaching Hispanic and Black PLWH.

### Eligibility criteria {10}

Individuals are eligible to participate in PATH if they meet the following criteria: (a) are at least 18 years old; (b) can read and speak English or Spanish; (c) are living with HIV and at least 3 months have passed since HIV diagnosis; (d) currently prescribed antiretroviral therapy (ART) medication; (e) have regular access to an Internet browser on a computer, tablet, or smartphone; (f) do not plan to move out of the San Diego area in the next 12 months; (g) not currently enrolled in any other program, intervention, or research study designed to improve HIV adherence or engagement in HIV care; and (h) not currently a member of one of the community advisory boards providing advisement on the study. In addition to criteria *a* through *g*, eligible participants must meet one or more of the following criteria: (1) one or more detectable VL test result (> 200 copies m/L) in the past 12 months while on ART for at least 3 months; (2) missed 1 or more scheduled HIV care appointments in the last 12 months; (3) last HIV care visit with an HIV care provider was more than 6 months ago; (4) report anything less than *excellent* adherence on one of the Wilson-3 ART adherence scale [28] items; and/or (5) report non-prescription stimulant or opioid use in the past 6 months. The first three indicators are verified using medical chart information, and the last two are assessed via self-report on the screening questionnaire. Finally, since the intervention was designed in a manner whereby the PATH peer navigators are meant to provide support as part of the HIV care team at the community-based FQHC, and as a study that is interested in exploring implementation outcomes of the PATH intervention, eligible participants are required to be current HIV medical care patients of the community-based FQHC.

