### Sample size {14}

It was estimated that a sample size of up to 375 total participants would be required to achieve study objectives. This estimate was informed by a sample size calculation. Figure 3 displays power and sample size estimates based on intervention effect sizes and covariates. Meta-analytic data from Finitsis et al. [44] of mHealth text messaging interventions to promote ART adherence among PLWH has shown that such interventions can improve VL suppression (*k* = 3; OR = 1.57, 95% CI = 1.11, 2.20). This OR of 1.56 is a small effect size, and Chen et al. [45] established conventions of small, medium, and large ORs (similar to Cohen’s magnitudes of effect size, *d*). Based on the Finitsis meta-analysis (OR = 1.57), and accounting for other possible effect sizes of small (OR = 1.68) or medium (OR = 3.47) magnitude (based on Chen et al.) [45], the required sample sizes to achieve adequate power of at least 0.85 ranges from *n* = 179 to 204; with covariates in the model (accounting for 25% of the variance in the outcome, then a sample size ranging from *n* = 263 to 339 would be required). To provide further support for this power analysis, we conducted another analysis in G*Power using an effect size estimate from a recent peer navigation intervention (that does not include a mHealth component, “LINK LA” [46]) for HIV-positive men and transgender women released from jail. In this study, the investigators tested the efficacy of their peer navigation intervention compared to usual care (case management) and found a 22% difference-in-difference between the intervention and control arm on viral suppression over a 12-month follow-up. Using this effect size information, and assuming 0.80 power, alpha = 0.05, and 1:1 allocation ratio between intervention and control arms, the required sample size is 97 per group, or a total *n* of 194. Altogether, our calculations to estimate the desired sample size with adequate power and, based on up to 20% anticipated attrition, a sample size between 225 and 375 would provide us with adequate power to achieve our aims. Thus, our goal is to randomize up to 375 participants for an analytic sample size of ~ 300 (150 per arm).

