### Methods for additional analyses (e.g., subgroup analyses) {20b}

In an effort to conduct a robust, comprehensive evaluation of the PATH intervention, moderator and mediation analyses will be conducted following primary outcome analysis. Specifically, exploratory analyses will investigate baseline moderators of the direct effects of the PATH intervention on sustained viral suppression. Specifically, models will include the main effects of the study arm, moderator, and the moderator-by-study arm product term as predictors of the primary outcome in separate models for each moderator. The following moderators (subgroups) will be explored: (race ethnicity) Hispanic vs. Black participants, (substance use) reported using non-prescription stimulants/opioids at baseline vs. not, (sex as biological variable) males vs. females, (gender) men (cis and trans) vs. women (cis and trans) vs. nonbinary, (mode of transmission/risk group) men who have sex with men (or trans women who have sex with men) vs. heterosexual vaginal or anal sex vs. injection drug use, and the other plausible moderators. Causal mediation analysis using the potential outcomes (counterfactual) framework [68, 69] will be used to examine hypothesized mediators of intervention efficacy. It is hypothesized that even if there is an absence of a total effect of the intervention on the primary or secondary outcomes, there will be indirect effects of the PATH intervention (compared to control) through the mediators listed in Fig. 1.

To explore substance use-related outcomes, which is one of the study objectives, the same intention-to-treat approach will be applied to the primary outcome analyses. We will explore whether the PATH intervention (compared to control) significantly reduced the frequency of substance use (e.g., from using almost every day to once a week), drug cravings (urge for continued use), number of sex acts in the context of substance use in the past 3 months, and/or engagement in substance use treatment.

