## Discussion

The PATH intervention integrates peer navigation and mHealth technology into a unified, scalable intervention that could both strengthen the impact of peer navigation on HIV care outcomes among PLWH, and simultaneously reduce the amount of implementation resources needed to support peer navigation in clinical settings. Not unlike other studies focused on marginalized populations, the challenge that we anticipated and have encountered thus far is with recruitment [70]. We originally aimed to recruit and enroll at least 15–16 new participants each month across 24 months. Instead, the enrollment rate on average has remained at a steady 11–12 new participants per month. By definition, the population from which we are trying to recruit are individuals who are poorly engaged in HIV care, or who are at risk of falling out of care. Additionally, the trial faced the unique factors associated with a trial launch during a global pandemic. Recruitment began in November 2021, during historically high rates of COVID-19 due to the Omicron variant [71]. Another historical factor affecting recruitment was the outbreak of MPOX in the summer of 2022 [72]. However, we believe that recruitment has been successful overall given the fact that it has continued at a consistent rate in the context of these unprecedented environmental challenges. Thus, in August 2023, the decision was made to extend the recruitment period to 30 months (+ 6 months).

Study retention and loss to follow-up are other factors of concern, since this is known to potentially lead to biased results in RCTs [73, 74]. As described in our analytic approach, we will account for any characteristics associated with loss to follow-up during analysis. Prior to that, we are making every effort to promote retention and minimize loss to follow-up, with the goal of maintaining at least 80% retention at each study visit. We expect to meet this threshold, owing in large part to the dedicated staff overseeing study retention. These staff are not only highly trained but are also employed by the community-based FQHC where the trial is being conducted, potentially minimizing any distrust of researchers that is often found especially in marginalized and racial/ethnic minority communities [75, 76].

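### The entry rule admits people who are already virally suppressed, yet suppression at entry is not named as a covariate or moderator, so a pooled result would mix achieving with maintaining suppression

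*Protocol article*

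**What the plan says.** All entrants must be current HIV patients of the clinic and prescribed ART. Beyond that, Eligibility criteria {10} states that "eligible participants must meet one or more of the following criteria: (1) one or more detectable VL test result". That first indicator reads in full "one or more detectable VL test result (> 200 copies m/L) in the past 12 months while on ART for at least 3 months". The others include "missed 1 or more scheduled HIV care appointments in the last 12 months" and the instruction to admit those who "report anything less than *excellent* adherence on one of the Wilson-3 ART adherence scale" items. The remaining two are a last HIV visit more than six months ago and recent stimulant or opioid use. The chart is used to verify the first three.

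Outcomes {12} defines the primary outcome as a viral load under 200 copies/mL at both 6 and 12 months. It is a status, not a change from baseline.

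Statistical methods {20a} names no baseline covariate for the primary model. Covariates enter if arms, or retained and lost participants, prove imbalanced. Under additional analyses {20b}, "exploratory analyses will investigate baseline moderators of the direct effects of the PATH intervention on sustained viral suppression". The list names race/ethnicity, substance use, sex, gender and transmission group, then closes with an open reference to further plausible moderators. Baseline viral load is also absent from the stratification statement in {16a} and from the baseline measures in {18a}.

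**The concern.** Suppression at entry is the baseline value of the primary outcome, and the entry rule lets it vary freely. In a person unsuppressed at entry, success means achieving suppression. In a person already suppressed, it means not losing it. These are different effects and may differ in size.

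If suppressed entrants are common, the pooled estimate mainly describes maintenance, and a worthwhile effect in the unsuppressed could be diluted below detection. The split could still be examined afterwards under the open wording. But a subgroup picked after a null carries little weight, and that is when the question will be asked. The same holds for adjustment: a covariate chosen because arms look unbalanced is weaker than one named in advance for its link to the outcome.

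**Working it through.** **1. Does any entry route require a detectable viral load at enrolment?**

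| Indicator | Viral-load condition at entry |
|---|---|
| 1. A detectable result in the past 12 months | None; the latest result may be suppressed |
| 2. Missed appointment | None |
| 3. Last visit over 6 months ago | None |
| 4. Adherence below the top answer | None |
| 5. Stimulant or opioid use | None |

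No route requires it.

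**2. How far could an effect be diluted? (illustration)** The article gives no share suppressed at entry and no control-arm rate.

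- From Sample size {14}: 375 × 0.80 = 300 analysed, 150 per arm; the 22-point figure, treated here as a simple difference; alpha 0.05 (two-sided is my assumption).
- Assumed: share *s* suppressed at entry; control-arm sustained suppression 0.90 in the suppressed and 0.40 in the unsuppressed; PATH adds 22 points in the unsuppressed and nothing in the suppressed.

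Control rate = 0.90*s* + 0.40(1 − *s*). PATH rate = 0.90*s* + 0.62(1 − *s*). Difference *d* = 0.22(1 − *s*). Power = Φ[(*d* − 1.96·SE0)/SE1], with SE0 pooled and SE1 unpooled.

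| *s* | Control | PATH | Difference | Power |
|---|---|---|---|---|
| 0% | 0.400 | 0.620 | 22 points | 0.97 |
| 50% | 0.650 | 0.760 | 11 points | 0.55 |
| 70% | 0.750 | 0.816 | 6.6 points | 0.28 |
| 80% | 0.800 | 0.844 | 4.4 points | 0.17 |

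The assumption that suppressed entrants cannot gain drives this table. If they gained 5 points at *s* = 80%, the difference would be 0.2 × 22 + 0.8 × 5 = 8.4 points (0.800 vs 0.884) and power 0.51.

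**3. What would the pooled data show?** The 95% half-width for the control rate is 1.96·√[p(1 − p)/150]: 7.8 points at p = 0.60 and 4.8 at p = 0.90. A ceiling would therefore be visible.

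The location of the effect would not be. At *s* = 80%, two different truths give the same pooled 0.800 vs 0.844:
- 22 points in the unsuppressed and 0 in the suppressed: 0.2 × 22 + 0.8 × 0 = 4.4.
- 2 points in the unsuppressed and 5 in the suppressed: 0.2 × 2 + 0.8 × 5 = 4.4.

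Only results split by suppression at entry separate them.

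**4. How precise would the split be?** Assume an odds ratio of 1 in the suppressed and control rates of 0.85 and 0.40. The variance of the log-odds-ratio interaction is the sum of 1/[n·p(1 − p)] over the four cells. For *s* = 50% and an odds ratio of 3.47 in the unsuppressed (PATH rate 0.698), with 75 per cell:

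2/(75 × 0.85 × 0.15) + 1/(75 × 0.40 × 0.60) + 1/(75 × 0.698 × 0.302) = 0.209 + 0.056 + 0.063 = 0.328; SE = 0.573.

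Power = Φ(1.244/0.573 − 1.96) = 0.58. Over *s* = 50% to 80%, power is 0.48 to 0.59 for an odds ratio of 3.47 and 0.13 to 0.15 for 1.68.

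For 0.40 vs 0.62 in the unsuppressed, the half-width 1.96·√[(0.40 × 0.60 + 0.62 × 0.38)/n] is about 16, 20 and 25 points with n = 75, 45 and 30 per arm (*s* = 50%, 70%, 80%).

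**The case against.** A reader might infer that suppressed entrants fall outside the trial's question, or that PATH cannot help them. The documents do not support this. The Discussion says "the population from which we are trying to recruit are individuals who are poorly engaged in HIV care, or who are at risk", and the rest of that sentence shows that the risk meant is disengagement, so maintenance in at-risk patients is part of the aim. The outcome requires suppression at both time points, and {20a} counts a missing viral load as failure, so a suppressed entrant can still fail by rebound, disengagement or a missed test. This stands, and it limits the dilution table to an illustration.

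A reader might also infer that a null could not be told apart from a lack of room to improve, or would be uninterpretable. That goes too far: the control-arm rate would show a ceiling. It would not show whether PATH worked in the unsuppressed.

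The moderator list is open, so nothing forbids the analysis, and an unseen analysis plan may name it. That lowers the weight of the point. Still, the article names five moderators and leaves out the baseline value of its own primary outcome.

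A further tempting step is to fault the 22-point planning figure as coming from another population. The article presents that calculation as supporting evidence and already says it was "for HIV-positive men and transgender women released from jail", so no rewording is asked for.

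Finally, one more exploratory moderator will seldom settle a null result. Step 4 confirms this. The gain is a pre-specified estimate with an honest interval, not a powered test.

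**Conclusion.** The point holds in a limited form. It is certain from the text that the entry rule admits people already suppressed, that the outcome mixes achieving with maintaining suppression, and that suppression at entry is not named as a covariate or specified moderator. The consequence is a pooled null that is harder to interpret, not one without meaning. Its size cannot be fixed from the article. Under the assumptions in step 2, the pooled effect shrinks from 22 points to between 11 and 4.4 as the suppressed share rises from 50% to 80%, and by less if suppressed entrants also benefit. This is an improvement the plan should make; it does not undermine the design.

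**What to change.** In Statistical methods {20a}, pre-specify suppression at entry as a covariate in the primary model. Define it by the most recent chart viral load before randomisation, under 200 versus 200 copies/mL or more, and state how participants with no such result are classed. In {20b}, name it as the first exploratory moderator. Report the arm effect with its confidence interval separately for participants unsuppressed at entry (achieving) and suppressed at entry (maintaining), labelled exploratory and imprecise.

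The cost is one covariate, one interaction model and one table. The chart is already read for viral load to verify the first indicator, and {26b} has participants authorise release of viral-load reports. Eligibility, recruitment and the intervention stay as they are. The downside is low precision: interaction power was below 0.60 in every scenario tried, so a non-significant interaction must not be read as equal effects.
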